**Sample size for qualitative study**

The sample size for the qualitative study will be determined based on the saturation of information. However, for a planned purpose, 12 in-depth interviews which is among religious leaders will be considered.

## 4.9 Randomization and Sampling procedure

First, 2 districts out of the 13 districts in Hadiya zone are selected purposely. Second, Non-adjacent 12 kebeles (clusters) are selected from two districts randomly. A pregnancy test will be done for the study women at the beginning of the surveillance. Then identified pregnant women with gestational age less than 20 weeks will be included in the study.

**For qualitative study:** A purposive sampling technique will be used to select the study participants for the in-depth interviews. Participants (religious leaders) will be selected based on their acceptance by their followers from each religion domination.

## Randomization

There are a total of 12 clusters for this cluster randomized trial. The researcher and kebele leaders, religious leaders and HEWs will conduct the randomization to produce comparable groups and eliminate the source of selection bias in the assignment of kebeles to the intervention and control groups. Simple randomization with a 1:1 allocation will be applied to assign clusters to either control or intervention groups. First, 12 nonadjacent clusters will be selected by a lottery method. Then, the 12 clusters were listed alphabetically. A list of random numbers will be generated in MS Excel 2010 and the generated values will be fixed by copying them as “values” next to the alphabetic list of the clusters. These are arranged in ascending order according to the generated random number. Finally, the first 6 clusters will be selected as intervention clusters and the last 6 as control clusters. A statistician that will be blinded to study groups and not participated in the trial will do the generation of the allocation sequence and the randomization of clusters (Figure below). The intervention group is assigned to receive training from religious leaders on maternal and neonatal health and the control group will be left to continue the current practices.

**Controlling contaminations and spill-over effects**

First, two districts are selected purposely from 13 districts in the Hadiya Zone. From two selected districts, 12 non-adjacent clusters are purposely and the clusters are allocated into either intervention or control group by simple randomization. The trained religious leaders will be assigned to provide intervention for pregnant mothers based on their residency of each cluster.

## 4.11 Trial design

This study is a parallel two-arm a cluster randomized controlled trial with 8 clusters. The trial arms are as follows: 1) religious leader training and 2) standard cares. The kebeles health posts are designated as clusters for the trial. Outcome assessments will be made using repeat cross-sectional surveys at baseline (prior to intervention roll-out) and at 4 months post intervention (i.e. the end line). A schematic for the trial design is displayed in Figure 2.

Screening

Two districts out of 13 districts of Hadiya Zone selected purposely

Non-adjacent 12 kebeles from two districts selected randomly

Randomization

Cluster randomization of 12 clusters to 2 study groups

Intervention groups: (6 clusters)

Control groups: (6 clusters)

Recruitment

-Recruit pregnant mothers with gestational age less than 20 wks. (n =341)

- Baseline data collection

base line data collection

**-**Recruit pregnant with mothers with gestational age less than 20 wks. (n =341)

-Baseline data collection

Intervention

Training for pregnant mothers by trained religious leaders

The usual care only

End line

End line data collection

End line data collection

Figure 2: Diagrammatic representation of the randomization of study cluster (kebeles)

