## 4.8 Sample size

In accordance with the main objective of the larger study, the sample size estimate is designed to detect changes in the proportion of skilled delivery service utilization. The sample size is calculated using stata software based on the following assumptions. Tail (s): One; effect size (d): 0.15; **α** error probability = 0.05; power (1-**β** error probability) = 0.8, and allocation ratio (N1/N2) = 1. This gives a sample size of 155. Then, adding design effect, DE = 1+(m-1)ICC , where m=Average cluster size, m= 50, ICC=0.02 based on a published study ICC (Killip et al., 2004), DE=2, and allowing for a 10% loss to follow up, the total sample size is 682 (N1 = 341 and N2 = 341). N1 and N2 are sample sizes in the control and intervention group, respectively. Based on these assumptions, the estimated sample size is: 306 pregnant mothers per group to detect a 15-percentage point anticipated difference in the proportion of skilled delivery service utilization (an increase from 26% to 41%). This estimate is based on the baseline skilled delivery service utilization in the Ethiopia Demographic and Health Survey (26% from EDHS 2016, SNNP region report) in the control group (CSA, 2016).

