## 4.17 Data collection and management

The principal investigator will train the data collectors and supervisors for two
consecutive days on instruction; in the quantitative method, study guides, role-plays
(demonstration), informed consent, how to approach participants, how to collect data using
mobile health, ethical procedure and general information and the objective of
the study. The data will be collected by using a mobile-based application called open data kit
(ODK). In the initial step, a pre-intervention survey will be conducted after the randomization and allocation. And there will be two times data collection including the pre-intervention and post-intervention data. The data will be collected by 4 months interval to have a good longitudinal data. The type of data will be panel data with repeated cross-sectional. Experienced data collectors with health background and Hadiyisa speaking will be recruited to collect the data. Besides, a master holder with health profession will be employed to supervise the whole data collection process.

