**Baseline Data Collection**

Six clinical nurses for data collection and two supervisors with master holder in public health will be used. Intensive training will be given for data collectors and supervisors on the item. The data collectors and the supervisors will be assigned to a different cluster of a given district. Interviews are expected to last approximately 1 h and will be conducted in a quiet, private space at the homes of the women. If selected women are absent from their homes, interviewers will visit households up to three different days/times to attempt to interview them before the woman will be replaced with another randomly selected woman. The data will be collected for a total of 15 days.

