**End line Data collection**

The same procedure with the baseline data will be repeated to collect the end line data after one month of delivery. Six data collectors with health background will be used to collect the data. Two supervisors will be assigned to check for the daily activity, consistency, and completeness of the questionnaire and to give appropriate support during the data collection process. The data collectors and the supervisors will be assigned to a different cluster of a given district.

Qualitative Data collection

Focus group discussions and in-depth interviews among religious leaders and pregnant mothers will be conducted. Trained graduate research assistants will conduct Focus group discussions and in-depth interviews. Data will be collected by recording interviews by audiotape. Brief field notes will be taken during interviews. Field notes will be carefully taken during data collection and analysis. These notes will collect observations and assumptions about what will be heard or observed and personal narratives about what will be felt by the researcher during an interview.

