## 4.19 Statistical analysis

Data of baseline and end-line surveys will be combined and analyzed using Stata 14.1. Analyses will be based on the intention-to-treat principle and compared differences of the outcomes between the intervention and control at both individual and cluster levels. First, Univariate analyses will be performed to explore the characteristics of respondents. We then will use logistic regression with random effects to estimate the effect of the intervention on prenatal behaviour, adjusting for clustering. Generalized estimated equations (GEE) regression analyses adjusted for clustering will be used to test the effect of the intervention on promoting maternal health behaviour. We will repeat analyses for the primary and secondary outcomes adjusted for baseline differences by fitting an interaction term between study period (baseline vs intervention) and allocation in each model. Mixed-effects multilevel logistic regression model will be used to identify determinants of birth preparedness and complication readiness.

**For qualitative study:** The interviews will be recorded and transcribed verbatim. The transcripts will be thematically analyzed using the qualitative software program Atlas.ti 6.0. Two analysts will independently code the transcripts and subsequently review, discuss, and refine the coding schemes until consensus will be reached. Emerging concepts will be assessed using the constant comparative method from grounded theory. This means that when this concept will be identified, previously analyzed interviews will be reviewed in order to check if their content fitted into this concept. A final version of the code book will be then developed leading to identification of themes, and sub-themes. Coded transcripts will be further analyzed and summarized in narratives for each theme and sub-theme. Study findings will be presented, discussed, and validated in a stakeholder meetings conducted in regional and district health offices.

| S.no | Research objectives | Study populations | Study design | Data source | Major outcome variables | Analytic model |
| --- | --- | --- | --- | --- | --- | --- |

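### Outcome sampling is described both as repeated cross-sections and as a followed cohort, and as written the baseline replacement rule carries over to endline, so unenrolled, untrained women can enter the comparison

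*Protocol*

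**What the plan says.** Repeated cross-sections:
- The Summary says that outcomes come from a repeated cross-sectional household survey.
- Section 4.11 says "Outcome assessments will be made using repeat cross-sectional surveys at baseline" and again four months after the intervention.

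Followed cohort:
- The flow diagram in 4.11 recruits 341 women under 20 weeks per arm, surveys them, gives training or usual care, and surveys again.
- Section 4.13 directs the training at the sampled women and delivers it in four group sessions.
- Section 4.8 sizes the trial "allowing for a 10% loss to follow up".
- Section 4.17 wants longitudinal data at a four-month interval.

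The same paragraph of 4.17 then joins the two: "The type of data will be panel data with repeated cross-sectional".

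On absence, the Baseline Data Collection part of 4.17 allows visits on up to three occasions "before the woman will be replaced with another randomly selected woman". The End line Data collection part says "The same procedure with the baseline data will be repeated to collect the end line data", one month after delivery. Section 4.19 states "Analyses will be based on the intention-to-treat principle" and compares the arms at both individual and cluster level.

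**The concern.** The two designs need different fieldwork. A cohort returns to named women and counts those not found as missing. A repeated cross-section draws a new sample each round and has no loss to follow-up. A field team cannot do both, and the replacement rule belongs to only one of them.

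At baseline, before enrolment is complete, substituting a woman who is not at home does no harm. At endline it would. The outcome that sizes the trial is where and with whom a woman gave birth. One month after delivery, women not at home may have given birth elsewhere, moved, fallen ill or died, all of which are plausibly related to that outcome. Substitution would take them out of the comparison. In intervention kebeles it would also bring in women to whom the sessions were never offered.

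**Working it through.** **1. The plan's own figure.** Section 4.8 gives 26% versus 41%, "error probability = 0.05", power 0.80 and 1:1 allocation. With mean proportion 0.335, the pooled formula is n = [z(α)·√(2 × 0.335 × 0.665) + 0.842·√(0.26 × 0.74 + 0.41 × 0.59)]² / 0.15².
- Two-sided, z = 1.960: 154.2, so 155 per group, which matches the protocol.
- One-sided, z = 1.645: 121.4, so 122. The protocol's label, "Tail (s): One; effect size (d): 0.15", therefore does not match its own 155. I use two-sided 5% below.
- Design effect: 1 + 49 × 0.02 = 1.98, stated as 2. Then 155 × 2 × 1.10 = 341 per arm, which also matches.
- 155 × 1.98 = 306.9 and 341 × 0.90 = 306.9. So 306 is the number needed before the loss allowance, and about the number left after a 10% loss. This is cohort arithmetic.

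**2. Set-up for dilution.** Twelve kebeles, six per arm (the opening sentence of 4.11 says 8; the rest of the protocol says 12), give 12 − 2 = 10 degrees of freedom and a critical t of 2.228. Replacement keeps 341 women per arm, so the cluster size is 341/6 = 56.8. The design effect is 1 + 55.8 × 0.02 = 2.117, and the effective n is 341/2.117 = 161.1 per arm.

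Assumption: a share r of endline intervention women are untrained replacements at the control rate of 26%. The protocol gives no r; 10% echoes its loss allowance, and 20% and 30% show the range. Then p₂ = 0.26 + 0.15(1 − r), SE = √{[0.26 × 0.74 + p₂(1 − p₂)]/161.1}, λ = (p₂ − 0.26)/SE, and power comes from the noncentral t.

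| r | p₂ | Difference (points) | SE | λ | Power |
|---|---|---|---|---|---|
| 0 | 0.410 | 15.0 | 0.0519 | 2.89 | 74% |
| 10% | 0.395 | 13.5 | 0.0517 | 2.61 | 65% |
| 20% | 0.380 | 12.0 | 0.0515 | 2.33 | 56% |
| 30% | 0.365 | 10.5 | 0.0513 | 2.05 | 46% |

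A normal approximation gives 82%, 74%, 64% and 53%: higher levels, similar drops.

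**3. Losing women compared with replacing them.** If 10% are lost and not replaced, n = 306.9 and the cluster size is 51.15. The design effect is 1 + 50.15 × 0.02 = 2.003, and the effective n is 153.2. With the 15-point difference kept, SE = 0.0532, λ = 2.82 and power is 72%. So an unreplaced 10% loss costs about 2 points of power, and a replaced one about 9.

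**4. Effect on the planned model.** Section 4.19 also fits a period-by-arm interaction, whose precision depends on whether the same women appear twice. By normal approximation with 341 per arm per round, two-sided power for 15 points is 0.56 to 0.87 with independent samples, as an assumed between-round cluster correlation goes from 0 to 1. With the same women and an assumed individual correlation of 0.5, it is 0.67 to 0.99. These correlations are not in the protocol.

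**The case against.** **Endline replacement is inferred.** The rule stands under the baseline heading. The endline paragraph goes on to collectors, supervisors and daily checks and never mentions substitution, so the same procedure may mean only the interview procedure. That reading is possible. But nothing excludes the other one, and a supervisor following the two paragraphs in order would substitute.

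**Intention-to-treat survives.** A reader might infer that it fails altogether. It does not: kebeles are randomised, and analysing every endline woman by her kebele's allocation is intention-to-treat at cluster level, with dilution. What is lost is an individual-level analysis of the enrolled women, if absent women are exchanged for others.

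**Losses leave a trace.** A reader might also infer that the enrolled set could never be reconstructed. The Annex 1 form, used in both rounds, carries an Individual Id, the visit number and a code for absence at three visits. The fields exist; what is missing is an instruction not to substitute.

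**Dilution may be smaller.** Leaders teach members of their own religion, and the endline engagement scale asks about messages given in congregation, so some untrained women may be exposed. The power figures above are therefore the unfavourable end for any given r. Nothing in the protocol supports a scenario in which half the women are untrained.

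**A cross-section could also be valid.** It could, with its own endline eligibility and sampling rules and no loss allowance. The protocol has none of these, and its recruitment, training and sample size are built on a cohort.

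**Analysis sets can be left to the SAP.** Their definition can. Who is interviewed at endline is fieldwork, which the protocol itself fixes in two ways.

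**Conclusion.** The contradiction between repeated cross-sections and a followed cohort is explicit. The carry-over of replacement to endline follows from the text as written but is not stated outright. If it is applied, the expected difference falls by 1.5 points for each 10% of intervention women replaced, and power falls from about 74% to 65%, 56% and 46% at 10%, 20% and 30%. These figures assume no effect in untrained women, ICC 0.02, 341 per arm and a two-sided test on 10 degrees of freedom. The starting value below 80% comes from the small number of clusters and the larger cluster size, not from this problem. Any bias from selecting on absence comes on top and cannot be sized from the protocol. The point should be settled before endline fieldwork, because outcomes of women who were substituted and not traced may not be recoverable afterwards.

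**What to change.** - Reconcile the Summary, 4.11 and 4.17 to one design: the enrolled cohort that recruitment, training and sample size already assume.
- Under Baseline Data Collection, limit replacement to before enrolment.
- Under End line Data collection, state that only enrolled women are re-interviewed and that there is no substitution.
- Link the rounds by the Individual Id already on the form, and record the reason for each non-contact.
- Analyse all enrolled women in their kebele's arm, with non-contacts treated as missing.
- Do not fill missing births from a second source such as health extension worker records. The outcome is defined as reported by the woman, the protocol describes no such record of births, and these workers know the allocation.

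The cost is protocol wording and tracing instructions. Endline numbers may fall to about 306 per arm, which 4.8 already allows for and which costs about 2 points of power in the calculation above.

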## 4.12 Sampling techniques

Considering the number of kebeles that can meet the sample size, the study includes 12 kebeles. The kebeles (cluster at health post level) are randomly selected and assigned to the intervention and control groups). Distance among the kebeles is considered and some kebeles are left in between to serve as a corridor and avoid contamination from the religious leaders, and to minimize the likelihood of contact between religious leaders and thus the exchange of information among the groups.

## 4.13 Intervention

For 4 months, trial participants in the intervention group will receive behavioural change communication on maternal health, while those in the control group will receive usual care. In collaboration with HEWs, kebeles leaders and religious leaders, the researcher and field workers will arrange an appropriate training place in the intervention clusters to train sampled pregnant mothers on prenatal health behaviour. During the intervention period, Hadiyisa will be the language of communication (the local language).

**Recruiting and training of religious leaders**

Protestant, Orthodox, and Muslim are three religion domains in Hadiya Zone. First, the religious organizations in the study districts will be identified (table 1). Then the local religious leaders from each clustered kebele will be recruited based on religious educational status (educational status greater than or equal to diploma), acceptance by their followers and popularity, in collaboration with religious organization leaders, health extension workers, and kebele leaders. A total of 16 religious leaders will be recruited to be trainers of pregnant mothers. Then after the potential religious leaders are recruited, the two days training will be given for them. Recruited religious leaders are expected to give training on the topics (maternal health) for four sessions to promote healthy maternal behaviours for the members of their religion.

Table 1 Distribution of religious institutions in selected clusters (kebeles) in Lemo and Amaka districts

| s.no | Selected Clusters (kebeles) | Total population | Religious institutions | | | Total no. of Religious institutions |
| --- | --- | --- | --- | --- | --- | --- |
|  |  |  | Orthodox | protestant | Muslim |  |
| 1 | Gidasha | 5861 | 2 | 2 | 0 | 4 |
| 2 | Tinika | 5012 | 1 | 3 | 1 | 5 |
| 3 | Dima | 4428 | 1 | 3 | 1 | 5 |
| 4 | Geja | 3121 | 1 | 3 | 0 | 4 |
| 5 | Ushusha Bonka | 5457 | 1 | 2 | 1 | 4 |
| 6 | Borara | 3742 | 2 | 1 | 0 | 3 |
| 7 | Lambuda | 2567 | 1 | 2 | 1 | 4 |
| 8 | Lareba | 4378 | 1 | 3 | 1 | 5 |
| 9 | Bobicho | 2756 | 1 | 3 | 1 | 5 |
| 10 | Kalisha | 3492 | 0 | 3 | 1 | 4 |
| 11 | Shurmo | 3156 | 0 | 2 | 1 | 3 |
| 12 | Ambicho gode | 2867 | 1 | 3 | 1 | 5 |

The first training session will be conducted at the beginning of the intervention whereas the second session of similar content will be repeated after one month of the first intervention session and the third and fourth training sessions will be after one months of the second intervention session. After training sessions, every participant will receive a copy of the visual materials (posters) containing the key messages for promoting prenatal health behaviours. Direct, interactive and participatory learner and activity oriented instructional strategies will be delivered. Talks, group discussions, group work exercises, demonstrations, role plays, storytelling, simulation, case studies and problem-solving will be used to enhance knowledge, attitude, and behaviours on maternal and neonatal health (Table 2 shows over protocol of intervention).

Overall project coordination: by PI and co-PIs

Step 1:

Formative assessment: perception of mothers’ on engagement of religious leaders in promoting maternal health, and role of religious leaders in promoting maternal and child health: a qualitative exploration of religious leaders’ perspective

Baseline study: Intervention protocol development, data collection and analysis

Developing strategies and SBCC material flip chart, information card and poster and recruiting religious leaders

Randomization of the clusters in to intervention and control groups

Step 3: Pregnant mothers’ training by trained religious leaders

Training contents: Maternal health message contents, flip chart, poster, group education and group discussion

**Session 1:** Major causes of maternal and new-born Illness and death

**Session 2:** Focused Antenatal Care and danger signs during pregnancy

**Session 3:** BPCR and danger signs during labor and childbirth

**Session 4:** Components of PNC and Postnatal danger signs and neonatal danger signs

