## 4.15 Intervention assignment and masking

Randomisation is stratified by kebeles, with 12 clusters in the district allocated to either control or intervention in a public randomisation meeting. From each clusters (kebele), local stakeholders (HEWs, kebele leaders and religious organization leaders) are invited, a number is allocated to each cluster, the numbers are written on small plastic balls, and placed the balls in a dark bag. Each participant is asked to draw one ball from the bag and read out the cluster numbers out until all balls are picked. The cluster numbers are written on a sheet of paper in order of selection. Participants then place 12 pieces of paper numbered 1 to 12—each corresponding to a unique allocation sequence generated by an independent statistician—in the dark bag, and asked a participant to select a paper and read out the number. The corresponding sequence is then used to publicly allocate each cluster to one of two groups. Because of the nature of the intervention being tested, the intervention team could not be masked to allocation. The data collection team will be masked to allocation, both at the cluster and at the individual level. Blinding is done to control for bias as follows. The researcher does not inform the study interventions and hypothesis for the participants who participate during the randomization of the kebeles into study groups.

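### As worded, religious leaders are recruited before cluster randomisation and not only in the intervention arm, which puts the usual-care comparator at risk

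*Protocol*

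**What the plan says.** Section 4.13, under the heading on recruiting and training religious leaders, states: "Then the local religious leaders from each clustered kebele will be recruited based on religious educational status". Table 1, directly below, lists all 12 selected kebeles. The same text fixes the number: "A total of 16 religious leaders will be recruited to be trainers of pregnant mothers". It adds that recruited leaders get two days of training and are then expected to run four sessions. The recruiting is done with religious organisation leaders, health extension workers and kebele leaders.

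Figure 3 sets out the process. Step 1 lists, in this order, formative assessment, baseline study, "Developing strategies and SBCC material flip chart, information card and poster and recruiting religious leaders", and then "Randomization of the clusters in to intervention and control groups". Training of the leaders is Step 2.

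For the comparator, the Randomization section says "the control group will be left to continue the current practices", and the control-group paragraph in 4.13 excludes leader-led training there. On those attending the allocation meeting, section 4.15 says "The researcher does not inform the study interventions and hypothesis for the participants who participate during the randomization of the kebeles into study groups". For the qualitative interviews, section 4.9 says "Participants (religious leaders) will be selected based on their acceptance by their followers from each religion domination".

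**The concern.** The religious leader is the agent under test, so what happens to leaders in control kebeles decides what the control arm is. If leaders are recruited before allocation, the team cannot yet know which six kebeles are the intervention ones, and the recruitment sentence does not restrict it to them. Respected leaders in future control kebeles would be asked to become trainers of pregnant mothers. On the literal text they would also be trained, because every recruited leader is.

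The protocol itself treats leaders as the contamination route: section 4.12 leaves corridor kebeles between clusters to limit contact between religious leaders. Recruiting inside control kebeles would bypass that safeguard.

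Two further things are at stake. Trainers spent on control kebeles are not available in the intervention arm. And the statement in 4.15 about what meeting attendees are told would be hard to sustain.

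**Working it through.** **1. Order of steps.** Figure 3 lists leader recruitment before randomisation, both within Step 1. This evidence is limited. The figure survives only as flattened text, with Step 3 printed before Step 2. Its placing of baseline before randomisation also disagrees with other sections: the participant timeline has randomisation on 1 June 2022 and baseline from 5 June, and section 4.17 puts baseline after allocation, while section 4.14 dates baseline to May 2022. Those conflicts concern the baseline survey. On leader recruitment, Figure 3 is the only statement of timing relative to allocation, and nothing contradicts it.

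**2. Which kebeles.** The recruitment sentence covers each clustered kebele and stands beside a table of all 12. Where section 4.13 means the intervention arm only, as for the training places, it says so. As worded, recruitment is not limited to one arm.

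**3. Consequence if both are followed literally.** Inputs: 16 leaders, 12 kebeles allocated 6 and 6, and 341 women per arm (section 4.8 and Figure 2).
- Leaders per kebele: 16 / 12 = 1.3.
- Leaders expected in intervention kebeles if spread evenly: 16 × 6/12 = 8.
- Women per trainer: 341 / 8 = about 43, against 341 / 16 = about 21 if all 16 work in the intervention arm.
- The other 8 would be recruited and trained in kebeles where the control-group paragraph rules out leader-led training.

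**4. What the count of 16 suggests.** Assumption, not stated in the protocol: one leader for each religion that has an institution in a kebele. From Table 1, five kebeles have two religions present and seven have three.
- All twelve kebeles: 5 × 2 + 7 × 3 = 31 leaders.
- Six kebeles, minimum: 5 × 2 + 1 × 3 = 13. Maximum: 6 × 3 = 18.
- Number of ways to choose six of twelve: 924. Exactly 15 leaders needs three two-religion and three three-religion kebeles: 10 × 35 = 350 ways. Exactly 16 needs two and four: 10 × 35 = 350 ways. Together that is 700 of 924.

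The stated 16 therefore fits six kebeles and falls well short of 31. Section 4.15's fidelity paragraph also calls for equal numbers per arm from each district, and Table 1 does not mark districts. That would rule out some of the 924 splits, but the range of 13 to 18 still bounds the answer.

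**5. The allocation meeting.** Section 4.13 names three groups that help recruit leaders. Section 4.15 invites the same three groups from each cluster, and the Randomization section adds religious leaders. If recruitment comes first, people who helped pick trainers of pregnant mothers already know what the intervention is. The statement that the researcher does not inform them of it would then not describe what happened.

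**6. Formative interviews.** These are also in Step 1. Section 4.9 selects leaders by acceptance among followers, one of the criteria also used for trainers, and does not exclude the 12 trial kebeles. The interview guide asks whether they raise maternal health in sermons and home visits.

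**The case against.** The strongest reply is that the protocol never intended this. All 16 leaders are to train mothers, training places are arranged in intervention clusters, leaders serve the cluster where they live, and control kebeles get no leader training. Together with the count of 16, that points to recruitment in six kebeles. Table 1 may only show institutions being identified, which is not the same as approaching anyone. The order in a flattened figure is weak evidence of chronology, and the absence of an exclusion for formative interviewees does not show that they come from trial kebeles.

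Much of this stands as evidence of intent, but it does not rescue the wording. Recruiting only in intervention kebeles requires the allocation to be known, so on that reading Figure 3 and the recruitment sentence both need correcting.

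A reader might infer more than the documents support, in four ways:
- *That leaders receive intervention materials before allocation.* Step 1 develops the materials; leaders meet the content in Step 2 training, after the step containing randomisation.
- *That control leaders are already primed, so usual care has failed.* This is a risk under one reading of the text, not an established fact.
- *That allocation concealment is broken.* An independent statistician generates the sequences, which are drawn in public. Knowing who might teach does not reveal any kebele's arm. Only the non-disclosure to attendees is affected.
- *That a specific loss of power follows.* It would require the share of control women influenced, which no section gives.

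**Conclusion.** The concern holds as a conflict in the plan's wording with a real but unquantified risk to the comparator. As written, leader recruitment precedes randomisation and is not confined to the intervention arm. Taken literally, that conflicts with the control-group description and with the non-disclosure statement in 4.15, and leaves about 8 of 16 trainers in intervention kebeles if leaders are spread evenly. The more likely intent is intervention-only recruitment, on the assumption of one leader per religion present; that intent can be carried out only after allocation. Either reading requires a correction.

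Neither the amount of contamination nor the direction of bias can be fixed from the protocol. Approached control leaders who take up the topic would shrink the difference, and leaders who disengage after being passed over would inflate it.

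**What to change.** - In Figure 3 and the recruitment paragraph of section 4.13, place recruitment of leaders after cluster randomisation, and replace the reference to each clustered kebele with each intervention kebele. Before allocation, only list institutions or eligible leaders from records, without approaching anyone.
- While redrawing Figure 3, bring its order into line with the dates in section 4.14, the participant timeline and section 4.17, which also need reconciling with each other.
- In section 4.9, state that formative participants come from outside the 12 trial kebeles and outside the corridor kebeles of section 4.12. Anlemo district, already used for the pre-test in section 4.18, is one option. The other health-post areas in the two study districts are less suitable because they include the corridor.
- Reword the statement in section 4.15 so that it claims only what attendees will in fact not have been told.

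The cost is mainly wording and the order of steps, plus a short delay between allocation and leader training.
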